### **16.2. Audits and Inspections**

In addition to the routine monitoring procedures, a Good Clinical Practice Quality Assurance unit exists within Celgene Corporation. From time to time, representatives of this unit will conduct audits of clinical research activities in accordance with Celgene Corporation SOPs to evaluate compliance with Good Clinical Practice guidelines and regulations.

The Investigator(s) is required to permit direct access to the facilities where the study took place, source documents, CRFs and applicable supporting records of subject participation for audits and inspections by IRB/IECs, regulatory authorities (e.g. FDA, EMEA, TPP) and company authorized representatives. The Investigator(s) should make every effort to be available for the audits and/or inspections. If the Investigator(s) is contacted by any regulatory authority regarding an inspection, he/she should contact Celgene Corporation immediately.

### **16.3. Investigator(s) Responsibilities**

Investigator responsibilities are set out in the ICH guideline for Good Clinical Practice and in the US Code of Federal Regulations. Celgene Corporation or a representative will contact and select all principal investigators or co-investigators who in turn will select their staff. The investigator must give the monitor access to relevant records to confirm the above.

The Investigator(s) is responsible for keeping a record of all subjects who sign an Informed Consent Form and are screened for entry into the study. For those subjects who fail screening,

the reason(s) for exclusion must be recorded in the subject's source documents and on the Screening Log provided by Celgene Corporation.

No procedure/assessment/measurement/test other than those outlined here, or in the schedule of study assessments, is to be performed without the prior written approval of Celgene Corporation, or unless deemed by the investigator(s) as necessary for the subject's medical care.

Investigator(s) and/or authorized designee(s) must enter study data onto CRFs supplied by Celgene Corporation. The data on the CRF will be recorded in an anonymous manner to protect the subject's identity by using a unique identifier that will prevent personal identifiable information.

The Investigator(s), or a designated member of the Investigators' staff, must be available at some time during monitoring visits to review data and resolve any queries and to allow direct access to the subject's records (e.g., medical records, office charts, hospital charts, and study related charts) for source data verification. The CRFs must be completed as soon as possible after the subject's visit but no later than prior to each monitoring visit and be made available to the Celgene Corporation representative(s) so that the accuracy and completeness may be checked.

## **17. REGULATORY CONSIDERATIONS**

### **17.1. Institutional Review Board/Independent Ethics Committee Review and Approval**

The protocol for this study has been designed in accordance with the general ethical principles outlined in the Declaration of Helsinki (see Section 21.5). The review of this protocol by the IRB/IEC and the performance of all aspects of the study, including the methods used for obtaining informed consent, must also be in accordance with principles enunciated in the declaration, as well as ICH Guidelines, Title 21 of the Code of Federal Regulations (CFR), Part 50 Protection of Human Subjects and Part 56 Institutional Review Boards. Before implementing this study, the protocol, the proposed informed consent form and other information to subjects, must be reviewed by a properly constituted Institutional Review Board/Independent Ethics Committee (IRB/IEC). A signed and dated statement that the protocol and informed consent have been approved by the IRB/IEC must be given to Celgene Corporation before the study initiation. The names and occupations of the chairman and the members of the IRB/IEC must be supplied to Celgene Corporation.

The Investigator(s) will be responsible for preparing documents for submission to the relevant IRB/IEC and obtaining written approval for this study. The approval will be obtained prior to the initiation of the study.

A copy of the IRB/IEC approval for the protocol and the Informed Consent is to be provided to Celgene Corporation. The approval for both the protocol and informed consent must specify the date of approval, protocol number and version, or amendment number.

The Investigator(s) is responsible for notifying the IRB/IEC of any serious deviations from the protocol, or anything else that may involve added risk to subjects.

Any advertisements used to recruit subjects for the study must be reviewed and approved by Celgene Corporation and the IRB/IEC prior to use.

### **17.2. Protocol Amendments**

Any amendment to this protocol that seems appropriate, as the study progresses (e.g. affects safety or efficacy) will be agreed upon between the coordinating and/or principal investigator(s) and the Celgene Corporation study physician. Amendments will be submitted to the IRB/IEC for written approval before the implementation of the amended version. The written signed approval from the IRB/IEC should refer specifically to the investigator(s) and to the protocol number and title and mention any amendment numbers that are applicable. Amendments that are administrative in nature do not require IRB/IEC approval but will be submitted to the IRB/IEC for information purposes.

### **17.3. Informed Consent**

The Investigator(s) must obtain informed consent of a subject or his/her designee prior to any study related procedures as per Good Clinical Practices (GCP) as set forth in 21 CFR Parts 50 and 56 and ICH guidelines.

Documentation that informed consent occurred prior to the subject's entry into the study and of the informed consent process should be recorded in the subject's source documents. The original consent form, signed and dated by the subject and by the person consenting the subject prior to the subject's entry into the study, must be maintained in the Investigator's study files and a copy given to the subject. In addition, if a protocol is amended and it impacts on the content of the informed consent, the informed consent must be revised. Subjects participating in the study when the amended protocol is implemented must be re-consented with the revised version of the informed consent. The revised consent form, signed and dated by the subject and by the person consenting the subject, must be maintained in the Investigator's study files and a copy given to the subject.

#### **17.4. Subject Confidentiality**

Celgene Corporation affirms the subject's right to protection against invasion of privacy. In compliance with United States federal regulations, Celgene Corporation requires the Investigator(s) to permit Celgene Corporation's representatives and, when necessary, representatives of the FDA or other regulatory authorities to review and/or copy any medical records relevant to the study in accordance with local laws.

Should direct access to medical records require a waiver or authorization separate from the subject's statement of informed consent, it is the responsibility of the Investigator(s) to obtain such permission in writing from the appropriate individual.

## **18. DATA HANDLING AND RECORDKEEPING**

### **18.1. Data/Documents**

The investigator(s) must ensure that the records and documents pertaining to the conduct of the study and the distribution of the investigational product(s), that is, copies of CRFs and source documents, original documents, data, and records (e.g., hospital records; clinical and office charts; laboratory notes; memoranda; subject's diaries or evaluation checklists; pharmacy dispensing records; recorded data from automated instruments; copies or transcriptions certified after verification as being accurate copies; microfiches; photographic negatives, microfilm, or magnetic media; x-rays; subject files) and records kept at the pharmacy, at the laboratories, and at medico-technical departments involved in the clinical study are complete, accurate, and filed and retained.

### **18.2. Data Management**

Data will be entered into the clinical database. These data will be electronically verified through use of on-line checks during data entry, and through programmed edit checks specified by the clinical team. Discrepancies in the data will be brought to the attention of the clinical team, and investigational site personnel, if necessary, in the form of a Data Clarification Form (DCF). Resolutions to these issues will be reflected in the database. An audit trail within the system will track all changes made to the data. A quality control audit will be performed.

### **18.3. Retention of Records**

The investigator(s) must maintain records of all study documents and supporting information relating to the conduct of the study. This documentation includes, but is not limited to, protocols, case report forms, advertising for subject participation, adverse event reports, subject source data, correspondence with health authorities and IRBs/IECs, informed consent forms, investigator(s) curricula vitae, monitor visit logs, laboratory reference ranges, laboratory certification or quality control procedures and laboratory director curriculum vitae. Subject files and other source data must be kept for the maximum period of time permitted by the hospital, institution or private practice specified below. The study monitor must be consulted if the investigator(s) wishes to assign the study files to someone else, remove them to another location or is unable to retain them for a specified period.

For studies conducted in the United States under a US IND, the investigator(s) must retain the study records for a minimum of 2 years after a marketing application for the indication is approved, or for 2 years after the IND is withdrawn. If no application is filed, or if the application is not approved for the indication, the records are to be retained for two years after the investigation (i.e., the IND) is discontinued, and FDA is notified of that fact. For IND studies conducted outside the US, the investigator(s), must retain study records for the time period described above or according to local laws or requirements, whichever is longer. The monitor will inform the investigator(s) of the dates for retention. All study documents should be made available if required by relevant health authorities. For studies not conducted under the US IND, the investigator(s) records must be retained until at least 2 years after the last approval of a

marketing application in an ICH region and until there are no pending or contemplated marketing applications in an ICH region or at least 2 years have elapsed since the formal discontinuation of clinical development of the investigational product. These documents should be retained for a longer period if required by other applicable regulatory requirements.

## **19. PREMATURE DISCONTINUATION OF THE STUDY**

### **19.1. Single Site**

The responsible clinical Investigator as well as Celgene Corporation have the right to discontinue a single site at any time during the study for reasonable medical or administrative reasons.

Possible reasons for termination of the study could be, but are not limited to:

- Unsatisfactory enrollment with respect to quantity or quality
- Inaccurate or incomplete data collection
- Falsification of records
- Failure to adhere to the study protocol

### **19.2. Study as a Whole**

Celgene Corporation reserves the right to terminate this clinical study at any time for reasonable medical or administrative reasons.

Any possible premature discontinuation would have to be documented adequately with reasons being stated, and information would be issued according to local requirements (e.g., IRB/EC, regulatory authorities, etc.).

## 21. APPENDICES

### 21.1. ECOG Performance Status Scale ([Oken, 1982](#))

| Score | Description                                                                                                                                               |
|-------|-----------------------------------------------------------------------------------------------------------------------------------------------------------|
| 0     | Fully active, able to carry on all pre-disease performance without restriction.                                                                           |
| 1     | Restricted in physically strenuous activity but ambulatory and able to carry out work of a light or sedentary nature, e.g., light housework, office work. |
| 2     | Ambulatory and capable of all self-care but unable to carry out any work activities. Up and about more than 50% of waking hours.                          |
| 3     | Capable of only limited self-care, confined to bed or chair more than 50% of waking hours.                                                                |
| 4     | Completely disabled. Cannot carry on any self-care. Totally confined to bed or chair.                                                                     |
| 5     | Dead.                                                                                                                                                     |

## 21.2. Adverse Event

An adverse event (AE) is any noxious, unintended, or untoward medical occurrence occurring at any dose that may appear or worsen in a subject during the course of a study. It may be a new intercurrent illness, a worsening concomitant illness, an injury, or any concomitant impairment of the subject's health, including laboratory test values (as specified by the criteria below), regardless of etiology. Any medical condition that was present prior to study treatment and that remains unchanged or improved should not be recorded as an AE. If there is a worsening of that medical condition, this should be considered an AE. A diagnosis or syndrome should be recorded on the AE page of the Case Report Form rather than the individual signs or symptoms of the diagnosis or syndrome.

All AEs will be recorded by the Investigator(s) from the time of signing ICF to 28 days after the last dose. AEs will be recorded on the AE page of the CRF and in the subject's source documents.

### Abnormal laboratory values defined as adverse events

An abnormal laboratory value is considered to be an AE if the laboratory abnormality is characterized by any of the following:

- Results in discontinuation from the study.
- Requires treatment, modification/interruption of investigational product(s) dose, or any other therapeutic intervention.
- Is judged by the Investigator(s) to be of significant clinical importance.

If a laboratory abnormality is one component of a diagnosis or syndrome, then only the diagnosis or syndrome should be recorded on the AE page of the CRF. If the abnormality was not a part of a diagnosis or syndrome, then the laboratory abnormality should be recorded as the AE.

### Serious adverse event

A serious adverse event (SAE) is any AE which:

- Results in death
- Is life-threatening (i.e., in the opinion of the Investigator(s) the subject is at immediate risk of death from the AE)
- Requires inpatient hospitalization or prolongation of existing hospitalization
- Results in persistent or significant disability/incapacity (a substantial disruption of the subject's ability to conduct normal life functions)
- Is a congenital anomaly/birth defect
- Constitutes an important medical event

Important medical events are defined as those occurrences that may not be immediately life threatening or result in death, hospitalization, or disability, but may jeopardize the subject or require medical or surgical intervention to prevent one of the other outcomes listed above.

Medical and scientific judgment should be exercised in deciding whether such an AE should be considered serious.

Events not considered to be SAEs are hospitalizations which: were planned before entry into the clinical study; are for elective treatment of a condition unrelated to the studied indication or its treatment; occur on an emergency outpatient basis and do not result in admission (unless fulfilling other criteria above); are part of the normal treatment or monitoring of the studied indication and are not associated with any deterioration in condition.

If an AE is considered serious, both the AE pages of the CRF and the SAE Report Form must be completed.

For each SAE, the Investigator(s) will provide information on severity, start and stop dates, relationship to investigational product(s), action taken regarding investigational product(s), and outcome.

### **Classification of severity**

For both AEs and SAEs, the investigator(s) must assess the severity of the event. The severity of AEs will be graded based upon the subject's symptoms according to CTCAE, Version 4.0 ([http://ctep.cancer.gov/protocolDevelopment/electronic\\_applications/docs/ctcae4.pdf](http://ctep.cancer.gov/protocolDevelopment/electronic_applications/docs/ctcae4.pdf)). AEs that are not defined in the NCI CTCAE should be evaluated for severity according to the following scale:

Grade 1 = Mild

Grade 2 = Moderate

Grade 3 = Severe

Grade 4 = Life threatening

Grade 5 = Death

### **Classification of Relationship/Causality of adverse events (SAE/AE) to investigational product(s)**

The Investigator(s) must determine the relationship between the administration of investigational product(s) and the occurrence of an AE/SAE as Not Suspected or Suspected as defined below:

***Not suspected:*** The temporal relationship of the adverse event to investigational product(s) administration makes **a causal relationship unlikely or remote**, or other medications, therapeutic interventions, or underlying conditions provide a sufficient explanation for the observed event

***Suspected:*** The temporal relationship of the adverse event to investigational product(s) administration makes **a causal relationship possible**, and other medications, therapeutic interventions, or underlying conditions do not provide a sufficient explanation for the observed event.

### **Monitoring and reporting of adverse events**

All subjects will be monitored for AEs during the study. Assessments may include monitoring of any or all of the following parameters: the subject's clinical symptoms; laboratory, pathological, radiological, or surgical findings; physical examination findings; or other appropriate tests and procedures.

### **Immediate reporting of serious adverse events**

Any AE that meets the criterion for an SAE requires the completion of an SAE Report Form in addition to being recorded on the AE pages of the CRF. The Investigator(s) is required to ensure that the data on these forms is accurate and consistent. This applies to all SAEs, regardless of relationship to investigational product(s), that occur during the study, those made known to the Investigator(s) within 28 days after a subject's last dose of investigational product(s), and those made known to the investigator(s) at anytime that are suspected of being related to investigational product(s).

The SAE must be reported immediately (i.e., within 24 hours of the Investigators' knowledge of the event) to the Celgene Corporation Drug Safety by facsimile. An initial written report (prepared by the Investigator(s) using the SAE Report Form provided by Celgene Corporation) is to be faxed to Celgene Corporation Drug Safety (see below for contact information).

The SAE report should provide a detailed description of the SAE and include copies of hospital records and other relevant documents. If a subject has died and an autopsy has been performed, copies of the autopsy report and death certificate are to be sent to Celgene Corporation as soon as these become available. Any follow-up data will be detailed in a subsequent SAE Report Form, and sent to Celgene Corporation.

The Investigator(s) is responsible for informing the Institutional Review Board/Ethics Committee (IRB/IEC) of the SAE and providing them with all relevant initial and follow-up information about the event. The Investigator(s) must keep copies of all SAE information, including correspondence with Celgene Corporation and the IRB/IEC on file. All SAEs that have not resolved upon discontinuation of the subject's participation in the study must be followed until either the event resolves completely, stabilizes/resolves with sequelae, or returns to baseline (if a baseline value is available).

### **Pregnancies**

Pregnancies and suspected pregnancies (including a positive pregnancy test regardless of age or disease state) of a female subject or the female partner of a male subject occurring while the subject is on investigational product(s), or within 28 days of the subject's last dose of investigational product(s), are considered immediately reportable events. Investigational product(s) is to be discontinued immediately and the subject instructed to return any unused portion of the investigational product(s) to the investigator(s). The pregnancy, suspected pregnancy, or positive pregnancy test must be reported to Celgene Corporation Drug Safety by facsimile using the SAE Report Form.

The female should be referred to an obstetrician-gynecologist, preferably one experienced in reproductive toxicity, for further evaluation and counseling.

The Investigator(s) will follow the female subject until completion of the pregnancy, and must notify Celgene Corporation Drug Safety of the outcome of the pregnancy as a follow-up to the initial SAE report.

If the outcome of the pregnancy meets the criteria for immediate classification as an SAE (i.e., spontaneous or therapeutic abortion [any congenital anomaly detected in an aborted fetus is to be documented], stillbirth, neonatal death, or congenital anomaly [including that in an aborted fetus]), the Investigator(s) should follow the procedures for reporting SAEs (i.e., report the event to Celgene Corporation Drug Safety by facsimile within 24 hours of the Investigator's knowledge of the event).

In the case of a live "normal" birth, Celgene Corporation Drug Safety should be notified by facsimile within 24 hours of the Investigator's knowledge of the event.

All neonatal deaths that occur within 28 days of birth should be reported, without regard to causality, as SAEs. In addition, any infant death after 28 days that the Investigator(s) suspects is related to the in utero exposure to the investigational product(s) should also be reported to Celgene Corporation Drug Safety by facsimile within 24 hours of the Investigators' knowledge of the event.

If the female is found not to be pregnant, any determination regarding the subject's continued participation in the study will be determined by the Investigator(s) and the Celgene Corporation Medical Monitor.

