**During study participation and for 28 days following investigational product discontinuation**

*Female Patients:*

- WCBP with regular or no menstrual cycles must agree to have pregnancy tests weekly for the first 28 days of study participation and then every 28 days while on study, at study discontinuation, and at day 28 following investigational product discontinuation. If menstrual cycles are irregular, the pregnancy testing must occur weekly for the first 28 days and then every 14 days while on study, at study discontinuation, and at days 14 and 28 following investigational product discontinuation.
- At each visit, the Investigator must confirm with the WCBP that she is continuing to use two reliable methods of birth control at each visit.
- Counselling about pregnancy precautions and the potential risks of foetal exposure must be conducted at a minimum of every 28 days.
- If pregnancy or a positive pregnancy test does occur in a study patient, lenalidomide must be immediately discontinued.
- Pregnancy testing and counselling must be performed if a patient misses her period or if her pregnancy test or her menstrual bleeding is abnormal. Investigational product treatment must be discontinued during this evaluation.
- Women must agree to abstain from breastfeeding during study participation and for at least 28 days after investigational product discontinuation.

*Male Patients:*

- Counselling about the requirement for condom use during sexual contact with women of childbearing potential and the potential risks of foetal exposure must be conducted at a minimum of every 28 days.
- If pregnancy or a positive pregnancy test does occur in the partner of a male study patient during study participation, the investigator must be notified immediately.

Additional precautions

- Patients should be instructed never to give this medicinal product to another person and to return any unused capsules to the Investigator at the end of treatment.
- Female patients should not donate blood during therapy and for at least 28 days following discontinuation of lenalidomide.
- Male patients should not donate blood, semen or sperm during therapy or for at least 28 days following discontinuation of lenalidomide.

Only enough lenalidomide for one cycle of therapy may be dispensed with each cycle of therapy.

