**MALE:**

1. I counselled the Male patient regarding the following:
  - Potential foetal harm (Refer to item #2 in WCBP).
  - To engage in complete abstinence or use a condom when engaging in sexual intercourse (including those who have had a vasectomy) with a woman of childbearing potential, while taking lenalidomide, during dose interruptions and for 28 days after stopping lenalidomide.
  - Males should notify their study doctor when their female partner becomes pregnant and female partners of males taking lenalidomide should be advised to call their healthcare provider immediately if they get pregnant
  - NEVER share lenalidomide with anyone else.
  - Do not donate blood, semen or sperm while taking lenalidomide and for 28 days after stopping lenalidomide.
  - Do not break, chew, or open lenalidomide capsules.
  - Return unused lenalidomide capsules to the investigator.
2. Provide Lenalidomide Information Sheet to the patient.

Investigator/Counsellor Name (Print): \_\_\_\_\_  
(circle applicable)

Investigator/Counsellor Signature: \_\_\_\_\_  
\_\_\_\_\_/\_\_\_\_\_/\_\_\_\_\_

Date:

(circle applicable)

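### Sections 21.2 and 21.3 leave open whether the pregnancy stop covers a man whose partner is pregnant, and cetuximab in a pregnant subject; partner pregnancies are reportable but lack a matching follow-up duty

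*Protocol*

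**What the plan says.** Section 21.2 (Adverse Event), under Pregnancies, makes pregnancies and suspected pregnancies immediately reportable. It covers those "of a female subject or the female partner of a male subject occurring while the subject is on investigational product(s"); the window extends to 28 days after the last dose. The next sentence gives one action for everyone covered: "Investigational product(s) is to be discontinued immediately and the subject instructed to return any unused portion". The text on a pregnancy that is ruled out ("If the female is found not to be pregnant, any determination regarding the subject's continued participation in the study will be determined by") leaves the decision to the investigator and the sponsor's medical monitor. The duty to follow the pregnancy until it ends is written for the female subject.

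Section 21.3.1, the pregnancy plan for territories outside the EU, separates women from men:

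- Female patients: "If pregnancy or a positive pregnancy test does occur in a study patient, lenalidomide must be immediately discontinued". For a missed period, or an abnormal test or bleeding, testing and counselling are required, and "Investigational product treatment must be discontinued during this evaluation".
- Male patients: if a pregnancy or positive test occurs "in the partner of a male study patient during study participation, the investigator must be notified immediately".

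The counselling document in Section 21.3.2 follows the same pattern. Women are told to stop lenalidomide on becoming pregnant. For men the text reads "Males should notify their study doctor when their female partner becomes pregnant", with nothing on the man's own treatment.

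Section 10.3 uses investigational product as the term for lenalidomide and/or cetuximab.

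**The concern.** The stop in Section 21.2 follows directly on a sentence that covers both female subjects and partners, and it uses the term that elsewhere means both drugs. Read literally, it takes a man off everything he is receiving when his partner is pregnant or may be. The parallel bullets in Section 21.3.1 attach a stop to the woman's case and only a notification to the man's. A site working from that section could reasonably conclude that no stop applies to him, or that for a pregnant woman on the combination only lenalidomide is concerned.

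The choice of section matters in practice. The eligibility criteria (Section 9.1.3), the pregnancy-testing text (Section 13.2.7) and the footnotes to Table 2 send sites to Section 21.3 or 21.4, not to Section 21.2.

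At stake is what an affected subject receives and how a possible fetal exposure is tracked. The protocol says that a teratogenic effect of lenalidomide in humans cannot be excluded (Section 21.3.1) and that the drug is found in semen (Sections 21.3.1 and 21.4.1). Partner exposure is thus a risk that it already recognises. There is a secondary effect on data: scheduled tumor assessment ends at treatment discontinuation and only survival is collected afterwards (Sections 12.2.1 and 12.2.4). An affected subject's response confirmation and progression data would therefore depend on how the site read the rule.

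**Working it through.** No figure in the plan depends on this point, so there is nothing to recompute. The check is a comparison of the sections, case by case.

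1. **Female subject, pregnancy confirmed.** Section 21.2 stops investigational product(s). Sections 21.3.1 and 21.3.2 name lenalidomide and do not mention cetuximab. In Arm 2 of the POC part lenalidomide is the only product, so the texts agree there. They differ only for subjects on the combination: Phase 2a, POC Arm 1 and the Expansion part. Section 10.3 does not fill the gap. It allows lenalidomide to go on when cetuximab is stopped, but does not address the reverse.

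2. **Female subject, pregnancy suspected.** Section 21.2 stops investigational product(s). Section 21.3.1 also stops investigational product treatment while a missed period, abnormal test or abnormal bleeding is evaluated. There is no conflict. Within Section 21.3.1 itself, however, the stop is worded more broadly during evaluation than for a confirmed pregnancy.

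3. **Male subject, partner pregnant or possibly pregnant.** Section 21.2 read literally stops investigational product(s). Sections 21.3.1 and 21.3.2 require notification and are silent on his treatment. The two can be applied together (notify, then stop), but Section 21.3 gives no sign that a stop follows.

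4. **Reporting against follow-up in Section 21.2.** The reporting sentence covers female subjects and partners of male subjects. The follow-to-completion sentence covers female subjects only. The later sentences on pregnancy outcomes meeting the SAE criteria, normal live births, neonatal deaths and later infant deaths are not limited to subjects. Reporting of a partner's outcome is therefore expected, but no sentence obliges the investigator to follow her until there is an outcome to report.

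**Size.** The protocol gives neither the sex split nor a pregnancy rate, so no count can be derived from it. Affected subjects should be few among the up to approximately 220 planned.

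**The case against.** The strongest reply is that the sections do not contradict each other. Section 21.3 is a lenalidomide plan that applies alongside Section 21.2, so it is natural that it names lenalidomide. For a partner pregnancy, the notification it requires would trigger the Section 21.2 procedure. This largely stands, and it rules out several stronger readings:

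- A reader might infer that the same man stays on treatment under one section and leaves it under the other. No section says that he continues; Section 21.3.1 is silent.
- A reader might infer that Section 21.3.1 stops lenalidomide alone. It names lenalidomide but does not say that cetuximab goes on.
- A reader might count as a conflict that Section 10.6 does not list pregnancy. That section gives events sufficient for discontinuation and does not claim to be complete, and other sections allow discontinuation for any other reason.
- A reader might make the same argument from the European plan (Section 21.4), whose text for men does not mention partner pregnancy. Silence is not a contrary rule, Section 21.2 is not limited by region, and that plan's information sheet is not in the text available here.
- A reader might infer that partner outcomes go unreported. The later outcome sentences in Section 21.2 are general; the gap is confined to the follow-up sentence.

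What the reply does not answer is how a site should know that both sections apply together. It is sent to the pregnancy plan, where one bullet carries a stop and its counterpart does not. Nor does the reply say what happens to cetuximab, or why follow-up is narrower than reporting.

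**Conclusion.** The point holds as a wording inconsistency in a safety rule, with two open questions: whether the Section 21.2 stop is meant for a man with a pregnant partner, and whether it includes cetuximab for a pregnant subject on the combination. A separate gap is that the follow-to-completion duty in Section 21.2 is narrower than its reporting duty.

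The reason to act is subject and fetal safety and consistent conduct across sites, not statistics. Events are assumed to be rare. No effect on alpha, power, sample size or the primary analysis is shown or claimed, and the effect on response and PFS data is limited to the few subjects concerned. Which stopping rule is right is a clinical and safety decision that the documents do not settle and this review does not make.

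**What to change.** Reconcile the Pregnancies text in Section 21.2 with Sections 21.3.1 and 21.3.2. Treat pregnancy in a female subject and pregnancy in a male subject's partner as separate cases. For each, give one statement, identical wherever it appears, of what action applies and which product(s) it concerns. The sponsor's clinical and safety functions decide the content.

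Extend the follow-to-completion sentence in Section 21.2 to the pregnant partner, subject to her consent, so that it matches the reporting rule.

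The cost is amendment wording and a consent procedure for partners. No subjects or study visits are added, and the statistical design is unchanged.
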